##### Proportion of text messages read

At the final treatment session, participants were asked: “How often did you read the habit reminder text messages?” This item is rated on a 0–100% scale. This measure was added to the protocol 11 months into the study as a manipulation check.

### Procedure

We will recruit participants within the USA and Canada, with by far the most participants from the former. Recruitment efforts will include distribution of information about the study to doctors and health care clinics as well as advertisements in the community (e.g., outpatient medical and mental health clinics in the San Francisco Bay Area) and online (e.g., Facebook, Reddit, and Instagram). People who are interested in learning more will be directed to contact the UCB research staff directly by phone or email.

Prospective participants will verbally consent to an initial eligibility phone screen. If the participant is eligible to participate in the full study, they will be invited to the pre-treatment assessment. Informed consent will be obtained prior to starting the pre-treatment assessment via HIPAA-compliant DocuSign, mail, or in-person, if the participant prefers. The pre-treatment assessment will be completed virtually (i.e., phone or HIPAA-compliant Zoom). Informed consent and assessments will be conducted by assessors (i.e., UCB research staff). Assessors enter anonymized data collected from the pre-treatment assessment via a HIPAA-compliant Qualtrics survey.

Once the participant is enrolled, they will be randomly allocated to HABITs or HABITs + Texts (see Allocation section for more details). Both intervention arms include HABITs, which involve three 50-min individual weekly sessions followed by six 30-min individual weekly sessions. Sessions are completed virtually via HIPAA-compliant Zoom. Treatment is delivered by sleep coaches (i.e., UCB research staff who are trained and supervised by [name], [name], MD, and [name]). Only the HABITs + Texts group will receive the text messaging intervention. Text messages will be delivered for 6 weeks. The text messages are collaboratively written by the participant and the participant’s sleep coach (and reviewed and approved by [name] or MD). During treatment, sleep coaches will assist participants in completing treatment assessments using HIPAA-compliant Qualtrics.

At the conclusion of treatment, typically within 8–11 weeks, the post-treatment assessment will take place within 2 weeks of the final session. The follow-ups will take place 6 months and 12 months after the pre-treatment assessment. The post-treatment assessment, 6-, and 12-month follow-ups will be completed by assessors via phone or HIPAA-compliant Zoom, and anonymized data will be entered via HIPAA-compliant Qualtrics.

### Allocation

Participants will be randomized in a 1:1 parallel group design to each intervention arm through a computerized randomization sequence. Randomization is stratified by age (≤ 24, 25 +) and sex, as there is evidence that these variables can impact sleep and/or intervention outcomes [114, 115]. The planned stratified randomization is part of the generation of the randomization sequence. Randomization will be conducted by one project coordinator (i.e., UCB research staff). The assessors will be blind to the intervention arm of the participants.

### Sample size

The sample size was determined by power analysis (via G*Power 3.1). Two-tailed alpha of 0.05 with a Bonferroni-corrected alpha of 0.017 for each of the three aims. The effect size was drawn from prior research on text message health interventions (*d* = 0.60) [64, 116, 117]. To achieve 80% power, 128 participants will be needed to detect between medium-effect-size group differences. We added 20% to account for attrition, yielding 160 participants.

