## Planned analyses

### Preliminary analyses and missing data

Data will be audited for quality and completeness. Missing or aberrant data will be verified for maximal data integrity. We will evaluate the distributions of the outcome variables and ensure that all the assumptions of planned analyses (e.g., linearity, normally distributed residuals) are met.

As per the power analysis described, we plan to recruit 160 participants, which allows for 20% attrition. Intent-to-treat analyses will use all available data via maximum likelihood estimation and produce valid inferences if attrition depends on intervention group or on previous outcomes for the same participant [118]. Additionally, sensitivity analyses may be conducted using multiple imputation to address missing data (e.g., dropouts, every item is not completed). If dropout is related to other variables, they will be included as predictors in the model to reduce any bias due to non-random missing data.

For Aims 1–3, all models will control for stratification factors (i.e., sex, age) used during the randomization procedure. Prior to the main analyses, appropriate statistical tests will be used to examine pre-treatment (i.e., baseline) differences between groups (e.g., education, current living arrangement, relationship status) to ensure comparability of the two randomized conditions (HABITs vs. HABITs + Texts) at pre-treatment and adequacy of the randomization. These tests will not be used to select covariates in the intent-to-treat analysis [119]. Instead, the potential influences of pre-treatment differences will be evaluated as moderators (described below in Exploratory Aim 1).

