### Aims 1–3: Effectiveness outcomes of HABITs versus HABITs + Texts

For Aims 1–3, we will use intent-to-treat analyses, including all randomized participants as randomized in the analysis regardless of their adherence or completion of the assigned intervention. We will use multilevel modeling [120] to account for multiple observations over time (pre-treatment, post-treatment, 6-month, and 12-month follow-up) nested within participants. The level 1 equation captures within-person variation across time and will include dummy-coded time indicators (0 = pre-treatment, 1 = post-treatment, 2 = 6-month follow-up, 3 = 12-month follow-up) as predictors. The level 2 equation captures between-person variations in the intercept and slope of time and will include dummy-coded intervention condition (0 = HABITs, 1 = HABITs + Texts) and intervention-by-time interaction terms, as predictors. The parameters of interest will be significant intervention-by-time interactions at the 5% level (i.e., differences in intervention effects on change in outcomes from pre-treatment to post-treatment, pre-treatment to 6-month follow-up, and pre-treatment to 12-month follow-up). Significant intervention-by-time interactions indicate that the trajectory of change on outcomes is significantly different over time, comparing HABITs + Texts to HABITs. For Aim 1a, utilization of sleep health behaviors, as indexed by the Utilization Scale will be modeled as the continuous outcome variable. For Aim 1b, sleep health behavior habits, as indexed by the primary measure (SRBAI-US), secondary measure (Adapted SRHI – Primary), and other measure (Adapted SRHI – Secondary), will be modeled as the continuous outcome variables, separately. For Aim 2, sleep and circadian functioning, as indexed by primary measures (i.e., CSHS, CSM, PROMIS-SRI, and PROMIS-SD) and secondary measures (i.e., PSQI, Sleep Diary and Actigraphy [night-to-night variability in the mid-point of sleep]) will be modeled as the continuous outcome variables, separately. For Aim 3, the latent variables of health risk, as indexed by the primary measure (Adapted WSAS) and secondary measures (i.e., DASS, PROMIS-CF, BSSS, PROMIS-APS, PHQ, and EMA Composite Risk Score^8^), will be modeled as the continuous outcome variables, separately.

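### The 128 participants do not follow from the stated d = 0.60, two-sided alpha 0.017 and 80% power, and the medium-effect claim attached to them has no stated basis

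*Protocol article*

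**What the plan says.** All the inputs stand in the Sample size section of the protocol article.

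- **Alpha:** "Two-tailed alpha of 0.05 with a Bonferroni-corrected alpha of 0.017 for each of the three aims".
- **Effect size:** "The effect size was drawn from prior research on text message health interventions", with d = 0.60 in brackets. It is the only numerical effect size in the section.
- **Result:** "To achieve 80% power, 128 participants will be needed to detect between medium-effect-size group differences". No number is attached to the word medium.
- **Attrition:** 20%, giving 160. The section on preliminary analyses and missing data relies on this: "As per the power analysis described, we plan to recruit 160 participants, which allows for 20% attrition".
- **Software:** G*Power 3.1. The section does not name the test family, the number of measurements or a correlation.

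The Allocation section gives 1:1 randomisation. The analysis section for Aims 1–3 plans a multilevel model over four time points and sets a different level from the sample size section: "The parameters of interest will be significant intervention-by-time interactions at the 5% level".

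**The concern.** The paragraph prints its inputs and its result, so the two should match, and under the simplest test they do not. The result is also described by an effect label that does not obviously belong to the effect size just given. Someone reading the paragraph as written would take the trial to have 80% power for a medium effect after correction for three aims. If medium is read in the conventional sense, that is not what 128 participants give in a simple two-group comparison at 0.017. A null result for an aim could then be read as stronger evidence against a medium effect than it is.

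**Working it through.** **Inputs.** From the Sample size section: d = 0.60; two-sided alpha 0.017 (0.05/3 = 0.0167, rounded); power 80%; 128 before attrition; 20% attrition. From the Allocation section: 1:1, so 128 is 64 per arm. Assumed, because the article does not say: a two-sample t-test as the reference calculation, and d = 0.50 as the conventional meaning of medium.

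**Formula.** With n per arm, the noncentrality is d × √(n/2), the degrees of freedom are 2n − 2, and power is the probability that a noncentral t variable falls outside ± the critical value t(1 − alpha/2).

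**Step 1: try to reproduce 128 for 80% power.**

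| d | two-sided alpha | n per arm | total N | power at that n |
|---|---|---|---|---|
| 0.60 | 0.017 | 60 | 120 | 80.5% |
| 0.60 | 0.05 | 45 | 90 | 80.4% |
| 0.50 | 0.017 | 85 | 170 | 80.1% |
| 0.50 | 0.05 | 64 | **128** | 80.1% |

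Worked line for the stated inputs: at n = 60, noncentrality = 0.60 × √30 = 3.286, critical t (118 df) = 2.421, power 80.5%. At n = 59, power is 79.7%, so 60 per arm is the minimum. The normal approximation gives 2 × (2.387 + 0.842)² / 0.60² = 57.9, so 58 per arm or 116 in total. Neither method gives 128.

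Worked line for the match: at n = 64, d = 0.50 and alpha 0.05, noncentrality = 0.50 × √32 = 2.828, critical t (126 df) = 1.979, power 80.1%. At n = 63, power is 79.5%, so 64 per arm is exact.

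**Step 2: attrition.** 128 / 0.8 = 160. This step is right, so the discrepancy lies in the 128.

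**Step 3: what 128 delivers at alpha 0.017 (unadjusted two-group comparison, critical t = 2.419).**

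- d = 0.60: noncentrality 0.60 × √32 = 3.394, power 83.4%.
- d = 0.50: noncentrality 2.828, power 65.9%.
- Smallest d with 80% power: 0.577, or 0.58 rounded.
- If all 160 were analysed (80 per arm): 77.2% for d = 0.50 and 91.5% for d = 0.60.

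**Step 4: other routes to 128.** Each uses inputs that the article does not state.

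- Repeated-measures ANOVA, between-factors test, f = 0.25, alpha 0.017, two measurements, correlation 0.5. Noncentrality = f² × N × m / (1 + (m − 1) × r) = 0.0625 × 128 × 2 / 1.5 = 10.67; power 80.0% at N = 128.
- Analysis of covariance, d = 0.50, alpha 0.017, baseline correlation 0.5. Effective d = 0.50 / √(1 − 0.25) = 0.577; N = 128.
- d = 0.60 at alpha 0.0125 (0.05/4): N = 128.

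**Step 5: the planned test.** The intervention-by-time term compares change from pre-treatment. For a simple change score the effective effect is d / √(2(1 − r)), where r is the pre-post correlation. With 128 analysed at 0.017, for assumed correlations:

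| r | power, d = 0.50 | power, d = 0.60 |
|---|---|---|
| 0.3 | 49% | 67% |
| 0.5 | 66% | 83% |
| 0.7 | 89% | 97% |

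At r = 0.5 the change score has the same power as the unadjusted comparison, since √(2 × 0.5) = 1. With baseline adjustment by analysis of covariance, the range for d = 0.50 over the same correlations is 71% to 94%.

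**The case against.** The strongest reply has three parts.

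**The cause is not established.** A reader might infer that the Bonferroni correction was simply ignored and that the calculation was run at d = 0.50 and 0.05. The documents do not support stating this as fact. The article names the software but no test, and step 4 shows routes that keep 0.017 and still reach 128. The repeated-measures one also sits comfortably with the between-group wording. The 5% level in the analysis section fits a calculation at 0.05 but does not prove one. This part stands, and it limits what can be said about the cause. It does not rescue the paragraph: none of those inputs is printed, and the ones that are printed do not lead to 128 by a simple two-group calculation.

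**The trial is not shown to be underpowered.** A reader might also infer that true power is about 66%. That needs medium to mean d = 0.50, which the article never says; the word could have been meant for d = 0.60. At d = 0.60 an unadjusted comparison of 128 has 83% power, eight participants more than the t-test requires (128 − 120). Maximum likelihood would also use partial data from participants who drop out. This stands as well: 66% is a conditional figure, not the power of the trial.

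**A condensed article may leave software settings to the full protocol.** That would excuse missing settings. It does not excuse a stated effect size, alpha and result that disagree, or an effect label without a value.

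**Conclusion.** The point holds as an inconsistency in the sample size justification. The printed inputs give 120 by a two-sample t-test, against 128 in the text. The exact t-test match for 128 is d = 0.50 at an uncorrected 0.05, which is the simplest explanation and remains unproven. On an unadjusted comparison, 128 participants are enough for the only effect size stated (83% at 0.017). They reach 80% only from d = 0.58 upwards, so a claim of 80% power for d = 0.50 after correction would not be supported on that basis: about 66%, or 77% with all 160 analysed. These figures assume a two-group t-test and, for the last two, the conventional meaning of medium. For the interaction test actually planned, power turns on the pre-post correlation (about 49% to 89% for d = 0.50 with a change score at correlations of 0.3 to 0.7), so the t-test figures should not be presented as the power of that test. The two alpha levels, 0.017 for sample size and 5% for analysis, are a separate contradiction within the same justification.

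**What to change.** Keep N = 160 and rewrite the Sample size paragraph.

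1. State one effect size, one alpha and the test actually used. If it was a repeated-measures calculation, give the correlation and the number of measurements.
2. Restate the required number or the power so that it follows from those inputs. If a two-group t-test is kept as a benchmark, label it as such: with 128 analysed at two-sided 0.017, 83% for d = 0.60 and a detectable effect of d = 0.58.
3. Delete the medium-effect wording, or define it numerically and give its power at 0.017.
4. Reconcile the 0.017 in the Sample size section with the 5% level in the analysis section for Aims 1–3, so that the power statement and the tests use the same threshold.

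The cost is a paragraph of text and one aligned sentence in the analysis section, with no extra participants. The downside is that the stated power for a medium effect may become less favourable.

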### Data management and dissemination

All participant-identifiable data will be saved by the assessment team on a secure password-protected and HIPAA-compliant website. All participants will be assigned identification numbers. These identification numbers will then be used to link anonymized data that is collected via password-protected and HIPAA-compliant Qualtrics. When collecting assessments, assessors will enter the data into HIPAA-compliant Qualtrics. Participant-identifiable data is not shared with outside entities during or after the trial.

A Data Safety Monitoring Board (DSMB) has been formed to help prevent and manage adverse events. The DSMB will be convened on a bi-annual basis for the first year and annually thereafter. For each report, the number of participants screened, the number of participants entered, the number of participants dropping out with the reasons for discontinuing, participant descriptive information, and the number of adverse events or serious events will be reported. All adverse events or serious events will be reported to CPHS (i.e., Institutional Review Board), the DSMB, and NICHD. However, if safety issues arise, this schedule will be changed to monthly meetings. For each report, minutes will be kept.

Organizations not directly involved in the trial (e.g., NICHD, DSMB, Institutional Review Board) have the right to audit and, if such a situation arises, will determine the frequency and procedures for auditing. The project management team will regularly audit the monthly enrollment as well as the completeness and quality of the data.

Results from the trial, as well as analysis code, will be shared via peer-reviewed publications, professional conference presentations, and a summary newsletter for participants. Other than the authors and compliance with data-sharing agreements stipulated by the National Institutes of Health, no other entities have contractual agreements to access the final dataset.

### Roles and responsibilities

This trial is supervised by the principal investigator ([name]), who manages the assessment team, the sleep coaches, and the data management team. The principal investigator will meet with members of each team regularly as needed in addition to daily email communication. The assessment team will be responsible for the informed consent process and conducting assessments. The sleep coaches will be responsible for delivering treatment, devising the text messages, and assisting participants in completing treatment assessments. The data management team will be responsible for downloading, collating, and analyzing the data. The trial sponsor is University of California, Berkeley.^7^ Other than ethical approval for the study, the sponsor has no role or ultimate authority in study design; collection, management, analysis, or interpretation of the data; writing of the report; or the decision to submit the report for publication. Finally, there are no other individuals or groups (e.g., Trial Steering Committee or Stakeholder and Public Involvement Group) overseeing the study.

### Changes to preregistration

This study was preregistered on clinicaltrials.gov (identifier: NCT05167695) on December 22, 2021. Since the study start date (May 2022), six updates have been made to clinicaltrials.gov: (1) EMA data was removed from the 6-month and 12-month follow-up due to participant burden and insufficient resources, (2) sessions 4 to 9 of treatment could not be completed in 20 min and thus were updated to 30-min sessions, (3) two additional outcome measures were added as it became clear that participants were typically working on at least two habit bundles (i.e., Adapted SRHI for the primary and secondary habit bundles), (4) an additional outcome was added as a manipulation check (i.e., Proportion of Text Messages Read), (5) the inclusion criteria for eveningness was clarified to distinguish “night-to-night variation in sleep and wake times” as opposed to “sleep/wake times”, and (6) we removed season as a moderator as there is little empirical evidence to support or negate the role of season in treatment response. This decision also served to help minimize multiple comparisons.

## Planned analyses

### Preliminary analyses and missing data

Data will be audited for quality and completeness. Missing or aberrant data will be verified for maximal data integrity. We will evaluate the distributions of the outcome variables and ensure that all the assumptions of planned analyses (e.g., linearity, normally distributed residuals) are met.

As per the power analysis described, we plan to recruit 160 participants, which allows for 20% attrition. Intent-to-treat analyses will use all available data via maximum likelihood estimation and produce valid inferences if attrition depends on intervention group or on previous outcomes for the same participant [118]. Additionally, sensitivity analyses may be conducted using multiple imputation to address missing data (e.g., dropouts, every item is not completed). If dropout is related to other variables, they will be included as predictors in the model to reduce any bias due to non-random missing data.

For Aims 1–3, all models will control for stratification factors (i.e., sex, age) used during the randomization procedure. Prior to the main analyses, appropriate statistical tests will be used to examine pre-treatment (i.e., baseline) differences between groups (e.g., education, current living arrangement, relationship status) to ensure comparability of the two randomized conditions (HABITs vs. HABITs + Texts) at pre-treatment and adequacy of the randomization. These tests will not be used to select covariates in the intent-to-treat analysis [119]. Instead, the potential influences of pre-treatment differences will be evaluated as moderators (described below in Exploratory Aim 1).

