#### Secondary measures

##### Adapted self-report habit index – primary bundle to build (Adapted SRHI—Primary)

The Adapted SRHI—Primary will assess the habit strength of the primary bundle to build at each session during treatment, post-treatment, 6-month, and 12-month follow-up assessments. The original Self-Report Behavioral Automaticity Index (SRBAI) [70] is a 4-item automaticity-specific adaptation of the full Self-Report Habit Index (SRHI) [88]. The four items of the original SRBAI plus two items from the full 12-item SRHI (“I do frequently” and “That belongs to my (daily, weekly, monthly) routine”) will be added to assess the frequency and relevance to self-identity, the two other primary proposed characteristics of habit, in addition to automaticity [70]. In total, six items will each be rated on a 5-point Likert scale (1 = *strongly disagree*, 5 = *strongly agree*). Total sum scores range from 6 to 30, where higher scores indicate greater habit strength.

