##### Sleep diary and actigraphy

The Sleep Diary and Actigraphy will be used to calculate night-to-night variability in the mid-point of sleep for the Composite Sleep Health Score. The Sleep Diary is a self-report adapted version of the consensus sleep diary [90], to track subjective sleep for 7 days. The sleep diary will be collected at all assessments and at each session during treatment. The Actigraphy (Actiwatch® GT9X Link; Philips Respironics) will assess movement samples in 60-s epochs over a 7-day period. Actigraphy will only be collected at the pre-treatment and post-treatment assessments. The intra-individual variability will be calculated using the estimated within-subject standard deviation [91].

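### The Aims 1–3 model leaves out the diary and habit scores collected at each session, so its dropout-validity statement is wider than the model supports and its rule for adding predictors is unsafe for those scores

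*Protocol article*

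**What the plan says.** Under Preliminary analyses and missing data, the protocol article states: "Intent-to-treat analyses will use all available data via maximum likelihood estimation". It then says that these analyses "produce valid inferences if attrition depends on intervention group or on previous outcomes for the same participant". Two safeguards follow. Multiple imputation is optional: "sensitivity analyses may be conducted using multiple imputation to address missing data". The other is a rule for extra covariates: "If dropout is related to other variables, they will be included as predictors in the model to reduce any bias due to non-random missing data".

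The section on Aims 1–3 defines the model by "multiple observations over time (pre-treatment, post-treatment, 6-month, and 12-month follow-up) nested within participants", with dummy-coded time and arm-by-time terms.

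Two instruments are also recorded between pre- and post-treatment. On the diary: "The sleep diary will be collected at all assessments and at each session during treatment". The Adapted SRHI – Primary "will assess the habit strength of the primary bundle to build at each session during treatment, post-treatment, 6-month, and 12-month follow-up assessments". Table 4 confirms both and shows no pre-treatment Adapted SRHI. The article does not place the session values in the Aims 1–3 models or name them as auxiliary variables.

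**The concern.** Likelihood inference is protected against dropout that depends on earlier outcomes only when those outcomes are in the likelihood. For diary mid-point variability and the Adapted SRHI, the session values are earlier outcomes of the same participant, yet they are outside the model. For the questionnaire outcomes they are related information on progress that could explain who leaves.

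If participants leave the study because recorded progress is poor, and this happens differently in the two arms, the arm-by-time contrasts are biased although data that could correct this were collected. A difference between arms is plausible, because only one arm receives texts in weeks 3 to 8.

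The written remedy is also awkward. Session scores are obvious candidates for variables related to dropout, but from session 4 on they are measured after the texts have begun. Entering them as covariates conditions on something the texts may already have changed.

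**Working it through.** **The plan's own figure.** The Sample size section allows 20% attrition on 128: 128 / 0.80 = 160, so 160 × 0.20 = 32 participants may be lost. That step reproduces. The article does not say how many of the 32 would leave during treatment, or why.

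**What is available for someone who leaves the study mid-treatment and misses every later assessment (Table 4)**

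| Outcome | In the four-assessment model | Recorded but unused |
|---|---|---|
| Utilization Scale, SRBAI-US, CSM, PROMIS-SRI, PROMIS-SD, Adapted WSAS | pre-treatment value | no value of the same measure; session diary and Adapted SRHI are related information |
| CSHS | pre-treatment value | session diary (source of 4 of its 6 dimensions) |
| Diary mid-point variability | pre-treatment value | session diary |
| Adapted SRHI – Primary and Secondary | nothing | session scores |

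**Size of possible bias.** All inputs here are assumptions except the effect of 0.60, which is the design effect size, and the overall 20% attrition.

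- Pre-treatment (Y0), session (M) and post-treatment (Y1) values are normal with SD 1, and higher is better.
- corr(Y0, Y1) = corr(Y0, M) = 0.5, and corr(M, Y1) = r.
- The arm difference is 0 in Y0, 0.30 in M and 0.60 in Y1.
- logit P(dropout) = c(arm) − slope × M. Slope 1 multiplies the odds of leaving by e¹ = 2.7 per SD of poorer progress. The constant c sets the dropout rate in each arm.
- Everyone who leaves is missing at post-treatment.
- Estimate without M: regress Y1 on arm and Y0 in those observed, predict for all randomised, take the arm difference and subtract the arm difference in Y0. Estimate with M: the same with M added to the regression.

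Estimates from 1,000,000 simulated participants per arm (truth 0.60):

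| Dependence on M | Dropout, HABITs / HABITs + Texts | r | Without M | With M |
|---|---|---|---|---|
| Same in both arms | 20% / 20% | 0.5 | 0.60 | 0.60 |
| Same in both arms | 20% / 20% | 0.7 | 0.60 | 0.60 |
| Same in both arms | 25% / 15% | 0.5 | 0.58 | 0.60 |
| Same in both arms | 25% / 15% | 0.7 | 0.56 | 0.60 |
| HABITs only | 20% / 20% | 0.5 | 0.56 | 0.60 |
| HABITs only | 20% / 20% | 0.7 | 0.52 | 0.60 |
| HABITs only | 25% / 15% | 0.5 | 0.55 | 0.60 |
| HABITs only | 25% / 15% | 0.7 | 0.50 | 0.60 |
| HABITs only, about half the attrition in treatment | 12% / 8% | 0.5 | 0.57 | 0.60 |
| HABITs only, about half the attrition in treatment | 12% / 8% | 0.7 | 0.55 | 0.60 |

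When dropout depends on arm and the pre-treatment outcome only, the estimate without M is unbiased (0.00). Harsher assumptions give more bias: up to −0.14 with slope 1.5 in HABITs only and r = 0.85, and up to −0.22 with opposite slopes in the two arms.

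**The predictor rule.** Suppose M enters the multilevel model with its own effect at each time, and there is no dropout at all.

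- The pre-treatment arm difference given M is 0 − 0.5 × 0.30 = −0.15, an imbalance created by the adjustment.
- The post-treatment arm difference given M is 0.60 − r × 0.30, which is 0.45 at r = 0.5 and 0.39 at r = 0.7.
- The arm-by-time contrast is 0.45 + 0.15 = 0.60 at r = 0.5 and 0.39 + 0.15 = 0.54 at r = 0.7.

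So the contrast loses part of the text effect whenever M is more closely tied to the later outcome than to the pre-treatment one. If M enters as a main effect only, complete data leave the contrast unchanged, but the false pre-treatment imbalance can still appear.

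**The case against.** Much of the case on the other side stands.

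A reader might infer that everyone who stops treatment is analysed on the pre-treatment value alone. The article does not support that. The Aims 1–3 section keeps all randomised participants whatever their completion, and the Procedure section times the 6- and 12-month follow-ups from the pre-treatment assessment. Only someone who leaves the study and misses every later assessment is in that position.

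A reader might also infer that the stated validity is not delivered at all. That is too strong. The sentence is conditional and is correct for dropout that depends on arm or on modelled outcomes. Six of the seven primary measures have no in-treatment value, so nothing of the same measure is discarded. A session CSHS cannot be computed, because Table 4 does not schedule the PROMIS items for satisfaction and alertness during treatment.

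The scenarios are assumed. Session scores come from different instruments than the questionnaires, so their correlation with those outcomes may be low; at r = 0.3 with HABITs-only dependence and 25% / 15% dropout the estimate is 0.59. With 64 per arm the unadjusted standard error is √(2/64) = 0.18 SD, so even −0.10 is about 0.6 of a standard error. In every biased scenario shown, the text effect shrinks, so a false benefit is not created.

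Finally, the choice of auxiliary variables is something an article may leave to an analysis plan that is not shown. That is fair, and the absence of such a list is not the point. What the article does state, the use of all available data, the validity sentence and the predictor rule, does not fit its own model and data schedule.

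**Conclusion.** The concern holds in a limited form. The claims about available data and previous outcomes reach further than a four-assessment model, most clearly for diary variability and the Adapted SRHI. The latter model receives nothing from a participant lost during treatment, and has no pre-treatment data for its reference time. The predictor rule would be a poor remedy if applied to session scores.

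Under the stated assumptions, with r between 0.5 and 0.7, the bias in the arm contrast is zero when dependence and dropout rates are equal across arms. It is about −0.02 to −0.10 SD on a true 0.60 when either differs, that is up to roughly 17% of the effect (0.10 / 0.60). Including the session value removes it. Because the article gives no dropout pattern, these figures show what is possible, not what is expected. This is a cheap improvement. It does not invalidate the primary analysis, and the session weeks need not be added to the primary likelihood.

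**What to change.** 1. Turn the optional multiple imputation into a planned sensitivity analysis, run separately by arm, with session Adapted SRHI scores and session diary summaries as auxiliary variables. Keep the three planned contrasts as they are. For the Adapted SRHI, state separately which time point serves as reference, since imputation does not supply the missing pre-treatment measurement.
2. Limit the rule on adding dropout-related predictors to variables measured before randomisation.
3. Reword the validity sentence: inference is valid for dropout that depends on arm or on the outcome values entered in the model. Align the statement on all available data with this.

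No new data are needed. The cost is a larger imputation model and some extra programming. The Trial status section has data collection running to July 2026, so the change should be fixed before outcomes are compared by arm.
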